#### Data source and collection

Data pertaining to key outcome measures and quantitative process indicators will be gathered using either paper-based or electronic CRFs. The CRFs will be developed by the WHO team in Geneva in collaboration with the country research teams. To refine the forms, advanced drafts will undergo testing with a suitable sample of service providers and simulated clients from the formative phase sites. Each health centre participating in the RCT will be assigned a research assistant who will receive training on adhering to the study manual and standard operating procedures for data management, developed by the WHO and consistent across both study countries. To ensure data quality, the accuracy and completeness of information recorded on the CRFs will undergo rigorous checks at multiple levels by field coordinators and data managers. This systematic approach will help maintain data integrity throughout the study period.

#### Data management

In line with protocols used in other multicenter studies sponsored by the UNDP/UNFPA/UNICEF/WHO/World Bank Special Programme of Research, Development and Research Training in Human Reproduction (HRP) at WHO in Geneva, a web-based data management system with be used for data entry and quality monitoring. HRP’s Biostatistics and Data Management team will develop this system using OpenClinica (V.3.16), an electronic data capture software designed for clinical research. OpenClinica includes programmed edit checks to ensure data quality, completeness and consistency, which helps in reducing delays associated with data queries and problem resolution, ensuring easy accessibility of the dataset. The OpenClinica system is a secure, open-source and reputable web-based software solution that fully adheres to Good Clinical Practice and regulatory guidelines, as well as the HRP/WHO standard operating procedures for clinical trial management

The country research teams in Pakistan and Nigeria will enter the data locally and have it reviewed by the WHO team in Geneva. We will provide training to the country teams on data entry and management using OpenClinica. The country research teams will be tasked with data verification, uploading data to shared files, and entering it into the OpenClinica system. To enhance accuracy, double data entry will be performed. The system is equipped with automated data query features to identify missing values, outliers, inconsistencies and other errors. The WHO team will oversee data quality monitoring. Any questions regarding data inconsistencies or missing values will be addressed through standardised forms sent to the sites, with continuous resolution of issues as they arise. To ensure data integrity and participant confidentiality, data transmission will be encrypted. Only approved users will be given access to the data, which will be password protected.

#### Statistical analysis

We will prepare a comprehensive statistical analysis plan. Participants will form the unit of analysis and the clustered nature of the data will be accounted for. All analyses will be by intention to treat. For continuous variables, we will compute means, SD, minimum and maximum values, and for categorical variables, we will compute frequencies and percentages. We will look at the distribution of variables and see if there are any outliers as part of data quality control and descriptive analysis. Descriptive statistics will be tabulated for individual clusters and aggregated across clusters. Within each of the three groups/arms of the study (two experimental and one control), outcome differences between final (12 months after enrolment) and intermediate (6 months after enrolment) outcome measurements will be obtained, and these changes will be compared between the control group and each of the two experimental groups. For categorical outcomes, χ^2^ tests for two independent proportions will be used, and for continuous variables, Student’s t-tests for two independent means will be used. We will use IBM SPSS Statistics 25, R V.3.6.2, STATA V.16.1 or SAS V.9.4 statistical packages for the analysis. The findings will be presented using the CONSORT Statement checklist from 2010 and its extension for cluster studies.^45^

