#### Outcome measures

Quantitative indicators will be captured in case-report forms (CRFs) developed and piloted at the country level before finalisation. The proposed outcomes to be assessed after each visit, at mid-point (6 months after enrollment) and at the study end (12 months after enrollment) are oriented toward clients and consist of levels of clients’ decision-making autonomy and demand satisfied for family planning.

To determine their level of decision-making autonomy, clients will be asked to answer questions about the different domains contained in the counselling definition (see the Background section). These domains comprise client–provider collaboration, client’s needs and preferences, the quality of information, freedom from coercion, confidentiality and dignity. The PCCC, developed and tested in publicly funded clinics in California, will also be used.^43^ The four PCCC questions fall under the domains of respect, eliciting—and giving serious consideration to—client’s preferences, and information quality and it will be assessed during the intervention phase as per described by UNFPA to measure decision-making autonomy SDG 5.6.1.^44^

The study proposes nonetheless the another outcome, while acknowledging its limitations: modern contraceptive prevalence after the first visit and at 6 and 12 months after enrollment.

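### As named, and unless the SAP adds imputation or a model using all measurements, the tests on the 12-minus-6-month change leave out women lacking either follow-up value

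*Protocol article*

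**What the plan says.** Under Statistical analysis, the protocol article says:

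- "We will prepare a comprehensive statistical analysis plan". That plan is not shown.
- "All analyses will be by intention to treat". The participant is the unit of analysis, and clustering is to be accounted for.
- The analysed quantity is a change within each arm: "outcome differences between final (12 months after enrolment) and intermediate (6 months after enrolment) outcome measurements will be obtained". Control is then set against either experimental arm on that change.
- Where the outcome is categorical, the article names chi-squared "tests for two independent proportions will be used". Where it is a measured score, the named method is Student's t-test on two independent means.

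Under Outcome measures, the client outcomes are "to be assessed after each visit, at mid-point (6 months after enrollment) and at the study end (12 months after enrollment"). Modern contraceptive prevalence is also recorded after the first visit and at 6 and 12 months. So information exists on women who later leave.

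The article gives no attrition rate and no rule for missing outcomes. Under Eligibility criteria, a woman must intend to be followed for 12 months and be willing to stay for the whole trial.

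**The concern.** With the woman as unit, a t-test on changes needs a change for each woman, and therefore a value at 6 and at 12 months. The named tests have no means of using a woman who has one of the two, or only an after-visit assessment. Without imputation, the analysed set is then fixed after randomisation by who stayed.

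Loss that differs by arm is plausible here. Participants and providers are not blinded, and the packages act on counselling quality and method choice, which could affect whether a woman returns. If it happens, the women compared are no longer the groups that were randomised, and the after-visit assessments that could help correct for this are not used by the named contrast.

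**Working it through.** **Inputs from the article.** 7920 participants; 36 sites in each of two countries; 1:1:1 allocation; assessments after visits and at 6 and 12 months.

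**Inputs assumed.** Loss rates, within-woman correlation and the loss mechanism. The article gives none of these.

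**The plan's own figure.** The article gives no sample-size inputs, so 7920 cannot be rederived from a formula. It is divisible as expected: 2 × 36 = 72 centres, 7920/72 = 110 women per centre, 7920/3 = 2640 per arm. This assumes that 7920 covers both countries and that centres are of equal size.

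**Women left out.** Let a be the share missing at each time. Nested losses keep 7920 × (1 − a); independent losses keep 7920 × (1 − a)².

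| a | Nested: kept / left out | Independent: kept / left out |
|---|---|---|
| 10% | 7128 / 792 | 6415 / 1505 |
| 20% | 6336 / 1584 | 5069 / 2851 |

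**Bias in the named contrast when loss depends on arm.** Take ratings with SD 1 at each time and correlation ρ between 6 and 12 months, and no true difference between arms. Let a standard normal loss score have correlation −0.5 with the 6-month rating; a woman is lost before 12 months if her score is in the top share d. Loss then depends only on arm and an observed value (missing at random).

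- Covariance of the change with the loss score: −0.5 × (ρ − 1) = 0.5 × (1 − ρ), which is 0.25 for ρ = 0.5 and 0.20 for ρ = 0.6.
- Mean loss score among women kept: −h(d), with h(d) = φ(c)/(1 − d) and c the normal quantile at 1 − d. This gives h = 0.109, 0.195, 0.350 and 0.497 for d = 5%, 10%, 20% and 30%.
- Absolute bias = 0.5 × (1 − ρ) × [h(d₂) − h(d₁)].

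| Loss in the two arms | ρ = 0.5 | ρ = 0.6 |
|---|---|---|
| 5% and 10% | 0.022 SD | 0.017 SD |
| 10% and 20% | 0.039 SD | 0.031 SD |
| 10% and 30% | 0.075 SD | 0.060 SD |
| 20% and 20% | 0 | 0 |

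A simulation with 2640 women per arm gave the same values to within 0.001 SD. A likelihood estimate using all 6-month values was within 0.001 SD of the true value in every row, with nearly the same standard error.

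**Standard error for comparison.** With 20% loss, 2112 pairs per arm remain. The change has SD √(2(1 − ρ)), so the standard error is √(2(1 − ρ)) × √(2/2112) = 0.031 for ρ = 0.5 and 0.028 for ρ = 0.6, if centre effects are stable over time and cancel from the change. A bias of 0.02-0.04 SD is thus roughly one standard error.

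**Loss not depending directly on arm.** In a simulation with 24 centres per arm, 110 women each, ICC 0.03, correlation 0.5 and loss driven by the last rating given, the change contrast moved by at most about 0.015 SD, although retention differed by 3-7 points between arms. A second missing-at-random check gave about 0.00-0.01 SD.

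**Loss depending on the unseen 12-month value.** With correlation −0.5 between the loss score and the 12-month rating and ρ = 0.6, the covariance is −0.5 × (1 − 0.6) = −0.20. Loss of 10% against 30% gives 0.20 × (0.497 − 0.195) = 0.06 SD, of the opposite sign to the case above; equal loss of 20% gives 0. The direction of any bias cannot be known in advance, and here a missing-at-random model would not remove it.

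**The case against.** The strongest reply is that this is an omission, not an error. The article condenses a fuller plan and promises an SAP, where rules for missing outcomes are commonly placed. That stands: the absence of such a rule is no finding. What remains concerns the contrast and tests that the article does fix, which a repeated-measures model in the SAP would have to replace.

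A reader might infer that the article contradicts itself by claiming intention to treat. It does not. In its narrow sense, intention to treat means analysis by allocated arm and is silent on absent outcomes. A reader might also infer that the plan is a complete-pairs analysis. The article never says so, and the same tests could be run on imputed data.

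It can be argued that the changes are differences of arm-level summaries, which need no pairs. That reading does not rescue the named tests: a two-sample test cannot be run on one summary difference per arm, and each summary would still omit women missing at that time.

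The plain tests also do not account for clustering, which the section promises, so the final method must come from elsewhere. This is a fair reason to keep the point conditional.

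Finally, the high discontinuation rates in the Background concern contraceptive use, not leaving the study, and the entry criteria favour women who mean to stay. Neither establishes how much loss to expect.

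**Conclusion.** The point holds conditionally. As named, and unless the SAP specifies imputation or a model using all measurements, the tests exclude women without both follow-up values and ignore the after-visit assessments.

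The size is modest and rests on assumed loss rates, correlations and mechanisms. Under missing-at-random loss, the bias in the named contrast is negligible (at most about 0.015 SD) if loss does not depend directly on arm. It is about 0.02-0.04 SD if loss clearly differs by arm, and exceeds that only with a gap as wide as 10% against 30%. The documents do not support a claim of serious bias. The case for change is that a better method costs almost nothing and makes the intention-to-treat statement apply to the women enrolled.

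**What to change.** In the Statistical analysis section and the SAP, replace the two-sample tests with a likelihood-based repeated-measures mixed model:

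- **Data:** every enrolled woman's recorded assessments after the first visit and at 6 and 12 months.
- **Terms:** arm, time, arm-by-time and trio; a centre random effect; and within-woman correlation, through a woman-level random effect or an unstructured residual covariance.
- **Yes/no outcomes:** a logistic mixed model with both centre and woman effects, or multiple imputation, or weighted GEE. Unweighted GEE is not generally valid under missing-at-random loss. A logistic model with only a centre effect would not use a woman's earlier answers to correct for her loss.
- **Reporting:** follow-up loss by arm; one sensitivity analysis that shifts missing 12-month values; any complete-pairs result labelled supportive.

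The cost is a change of wording and slightly more analysis work. No new data are needed, because the assessments are already scheduled. The downside is reliance on a missing-at-random assumption, which the data cannot confirm; the sensitivity analysis shows how far the conclusion depends on it.

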Building on this systematic review, the WHO organised a geographically diverse think tank in May 2019 in Geneva, Switzerland, to identify research and guidance gaps and other opportunities to improve the quality of contraceptive counselling.^32^ Equally important was the crafting of a definition on contraceptive counselling, which was adopted by think tank members^33^ : *Contraceptive counselling is defined as the exchange of information on contraceptive methods based on an assessment of the client’s needs, preferences and lifestyle to support decision-making as per the client’s intentions. This includes the selection, discontinuation or switching of a contraceptive method. The key principles are based on coercion-free and informed choice; neutral, understandable and evidence-based information; collaborative and confidential decision-making process; ensuring respectful care, dignity and choice*. The definition took into consideration the core dimensions articulated in the literature and mirrors the principles that were deliberated by the think tank: a two-way discussion and decision-making process between the client and provider, sharing objective and user-friendly information, and fundamentally grounded in the rights to autonomy, dignity, privacy, respect and participation, among others. In addition, person-centeredness is a critical component of quality in family planning.^5^ The four-item person-centred contraceptive counselling scale (PCCC) is a valid and reliable measure of person-centred contraceptive counselling that reflects patients’ perspectives on contraceptive counselling.^34^ For example, integrating Dehlendorf’s four-item validated tool: PCCC: person-centred contraceptive counselling scale: Think about your visit. How do you think the member of the healthcare team did? Please rate them on each of the following by circling a number (the scale will use—Poor, Fair, Good, Very good and Excellent). Hence, to measure decision-making autonomy, the following considerations need to factor:

Respecting me as a person.Letting me say what mattered to me about my birth control method.Taking my preferences about birth control seriously.Giving me enough information to make the best decision about my birth control method.

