The objective of the *experimental phase* is to assess, using a cluster randomised controlled trial (RCT) design, the impact of the contraceptive counselling bundle on clients’ level of decision-making autonomy and demand satisfied for family planning. The three-armed cluster RCT comprises (1) a control arm with contraceptive counselling and care and a range of family planning methods that are available at field level per the national policy and guidelines; (2) an experimental arm implementing the contraceptive counselling package but still with a range of family planning methods that are available (upto four methods) per the national policy and guidelines at field level and (3) another experimental arm with the contraceptive counselling package but with an expanded range of family planning methods (more than four methods) that are recommended by national policy and guidance.

The *reflective phase* objective is to determine operational barriers and catalysts related to the package implementation using qualitative research. Once the package of interventions has been identified—and resources permitting, we might consider conducting a cost-effectiveness analysis to determine the counselling package cost-effectiveness.

The qualitative research and cluster RCT are detailed in the following sections.

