#### Interventions

The primary health centres assigned to the first experimental group will implement the intervention package. Meanwhile, those in the second experimental group will implement the intervention package along with an expanded range of family planning methods recommended by national guidelines. The control group will continue with usual care practices.

Depending on the specific components of the intervention package, certain interventions, such as provider capacity building, may be implemented prior to participant recruitment to ensure readiness and effectiveness of the interventions during the study period.

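### The only between-arm comparison the article states, the 12-month minus 6-month change, estimates how the effect moves after month 6 and not the effect on outcome level that the trial sets out to assess.

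*Protocol article*

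**What the plan says.** The aim of the experimental phase, given under Study phases and timelines, is to assess "the impact of the contraceptive counselling bundle on clients’ level of decision-making autonomy and demand satisfied for family planning".

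The Outcome measures section lists when the outcomes are taken: "The proposed outcomes to be assessed after each visit, at mid-point (6 months after enrollment) and at the study end (12 months after enrollment". The further outcome is "modern contraceptive prevalence after the first visit and at 6 and 12 months after enrollment". In this text every outcome time comes after enrolment.

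Women enrol when they attend a family planning clinic to start, switch, resume or stop a method (Eligibility criteria). The Interventions section adds that some components, such as provider training, "may be implemented prior to participant recruitment to ensure readiness and effectiveness of the interventions during the study period". The package can therefore already be in place at a woman's enrolment visit.

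The Statistical analysis section then fixes the between-arm comparison. Its first step is taken inside each arm: "outcome differences between final (12 months after enrolment) and intermediate (6 months after enrolment) outcome measurements will be obtained". Its second step sets the arms against each other on that quantity: "these changes will be compared between the control group and each of the two experimental groups". The next sentence names the tests: χ² "tests for two independent proportions will be used, and for continuous variables, Student’s t-tests for two independent means will be used". It attaches no other time point or quantity to them. The section also promises a comprehensive statistical analysis plan, which is not available here.

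**The concern.** A change score helps when the earlier value is a baseline that treatment has not touched. Here the earlier value is taken six months after the woman was enrolled and counselled. Any effect already present at month 6 is subtracted from the effect at month 12.

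The trial's main conclusion is at stake. A package that works at once and keeps working would be reported as having no effect. One that keeps a clear advantage at both times, but a smaller one at month 12, would be reported as worse than routine care. The ratings taken after the visit do not enter the stated comparison at all. Yet the four-item counselling scale reproduced in the Background is worded for that moment ("Think about your visit. How do you think the member of the healthcare team did").

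**Working it through.** **Figures in the article.** The article gives no effect size, intracluster correlation (ICC) or attrition rate, so there is no planned power to reproduce. The sample-size counts do fit together: 36 sites in each of two countries is 72 sites, or 24 per arm. Reading 7920 as the total over both countries, 7920 / 72 = 110 women per site and 7920 / 3 = 2640 per arm.

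**Algebra of the stated contrast.** Let T and C be the experimental and control arm values, with subscripts for months.

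D = (T12 − T6) − (C12 − C6) = (T12 − C12) − (T6 − C6) = effect at 12 months − effect at 6 months.

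- Constant effect of any size: D = 0.
- Effect that shrinks but stays positive: D < 0.
- Effect that grows after month 6: D > 0.

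This needs no assumption about rates, correlation or clustering.

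**Illustration (all rates assumed).** The control arm is at 50% at both times unless noted. Other assumptions are two-sided 5%, 2640 women per arm, a within-woman correlation of 0.5, and a design effect of 1 + 109 × ICC applied to both contrasts. This gives design effects of 1, 2.09 and 6.45 for ICC 0, 0.01 and 0.05.

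Worked line, waning effect (experimental arm 65% then 58%) at ICC 0.01:

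- D = (58 − 65) − (50 − 50) = −7 points.
- Variance of change, control: 0.25 + 0.25 − 2 × 0.5 × 0.25 = 0.25.
- Variance of change, experimental: 0.2275 + 0.2436 − 2 × 0.5 × √(0.2275 × 0.2436) = 0.2357.
- Effective number per arm: 2640 / 2.09 = 1263.
- Standard error: √((0.25 + 0.2357) / 1263) = 0.0196.
- z = −0.07 / 0.0196 = −3.57, so the chance of a significant result against the package is Φ(3.57 − 1.96) = 0.946.

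All scenarios, with results in the order ICC 0 / 0.01 / 0.05:

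| Scenario | Effect at 6 mo | Effect at 12 mo | D | Power, 12-month level | D significant for package | D significant against package |
|---|---|---|---|---|---|---|
| Lasting (60%, 60%) | +10 | +10 | 0 | 1.000 / 0.999 / 0.821 | 0.025 at each | 0.025 at each |
| Lasting, both arms decline 5 points | +10 | +10 | 0 | 1.000 / 0.999 / 0.817 | 0.025 at each | 0.025 at each |
| Waning (65%, 58%) | +15 | +8 | −7 | 1.000 / 0.981 / 0.632 | 0.000 at each | 0.999 / 0.946 / 0.529 |
| Growing (55%, 60%) | +5 | +10 | +5 | 1.000 / 0.999 / 0.821 | 0.955 / 0.715 / 0.301 | 0.000 at each |

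Even when the effect grows, D shows only the 5 points gained after month 6, not the 10 points present at month 12. Its power is lower than that of the level comparison at every ICC shown.

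Applying the full design effect to D is cautious. Centre effects that are stable over time cancel in a change, so the waning result against the package could be more likely than shown.

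**The case against.** The best defence is that this is a condensed article with a full analysis plan promised. The named χ² test for two independent proportions fits a comparison of levels at least as well, since a woman's change in a yes/no outcome is not a proportion. That has some force: the text may describe the intended analysis poorly. But the test sentence follows directly on the comparison of changes and names no time point. The article is not silent here. It commits to a particular contrast, and if levels were meant the wording still has to be corrected.

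A second defence is that the section on the overall objective words the outcomes as changes, so analysing change is not foreign to the trial. This is true, but the difficulty is the reference time. Change measured from month 6 onward in women already counselled describes durability.

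A third is that the package was not yet designed and women are followed at the centre for 12 months, so repeated exposure could make the effect grow. That is possible, and the contrast would then point the right way, though it would still understate the effect.

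A reader might also infer three stronger things that the article does not establish:

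- *That this is the only comparison planned.* It is the only one stated in the article; the full plan may contain others.
- *That no pre-counselling measurement exists.* The text lists none, but the schedule of assessments is a figure not available here, and a woman's user status is known at entry. In any case the stated contrast uses no baseline.
- *That every woman missing either follow-up is dropped.* The article does not say that changes are paired within women or that incomplete cases are excluded, and it gives no attrition figure.

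**Conclusion.** The point holds, and the text must be corrected before outcomes are compared by arm. As worded, the stated comparison estimates the 12-month effect minus the 6-month effect. That is not the impact on the level of autonomy and on demand satisfied that the article gives as its objective. The cancellation and the reversal of sign are exact and rest only on both measurements being taken after the enrolment counselling visit.

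The size rests on the assumptions above. Under a lasting 10-point effect the stated test rejects only at its 5% false-positive rate, against power of 0.821 to 1.000 for 12-month levels. Under an effect waning from 15 to 8 points it is significant against the package with probability 0.529 to 0.999. The conclusion is confined to what the article states.

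**What to change.** In the Statistical analysis section and in the analysis plan:

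- Make the main comparison the difference in outcome level between each experimental arm and control at a pre-specified time. One option is 12 months, with 6 months and the post-visit rating as supportive. For decision-making autonomy the sponsor may prefer the post-visit rating as the main time; that is its choice, but it should be fixed in advance.
- Estimate it in a model with arm, time and arm-by-time that accounts for centres and for the matched trios, and that uses all available outcome values.
- Keep the 6-to-12-month change only as a secondary analysis, labelled as a question about durability.

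The cost is a reworded paragraph and a little more analysis. The outcomes are already scheduled at these times, so no new data, visits or participants are needed.

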**Methods:**

A multisite, two-stage and five-phase intervention design will start with a pre-formative, formative, design, experimental and reflective phase. The pre-formative phase will map potential study sites and establish the sampling frame. The two-part formative phase will first use participatory approaches to identify clients’ perspectives, including young couples and providers, to ensure research contextualisation and address each interest group’s needs and priorities followed by clinical observations of client–provider encounters to document routine care. The design workshop in the third phase will result in the development of a package of contraceptive counselling interventions. In the fourth experimental phase, a multi-intervention, three-arm, single-blinded, parallel cluster randomised-controlled trial will compare routine care (arm 1) with the contraceptive counselling package (arm 2) and the same package combined with wider methods availability (arm 3). The study aims to enrol a total of 7920 participants. The reflective phase aims to identify implementation barriers and enablers. The outcomes are clients’ level of decision-making autonomy and use of modern contraceptives.

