### Cluster RCT

The research will be a multi-intervention, three-arm, single-blinded, parallel, cluster RCT done in selected primary health centres (clusters) in Pakistan and in Nigeria (see figure 2 for the cluster RCT flow diagram, and figure 3 for the schedule of enrolment, interventions and assessments (Standard Protocol Items: Recommendations for Interventional Trials template). Centres will be randomly allocated to the three study arms in matched ratios (1:1:1) on the basis of the number of monthly family planning encounters, the number of available contraceptive types, the ratio of health workers per population in the clinic coverage zone, the location in urban or rural settings and selected district-level variables that may have an influence on the study outcomes, including the unmet need for family planning, the level of literacy among women and household income terciles. Only data analysts will be masked/blinded to trial-arm allocation. Service providers skilled in family planning services will implement the clinical components of the contraceptive counselling package.

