#### Randomisation

In each country, a total of 36 sites will be selected and matched into 12 trios based on the specified criteria. Within each trio, the study sites will be randomly assigned to one of three study arms at a 1:1:1 ratio. This randomisation process will be repeated 12 times, once for each trio. The randomisation process will not have any restrictions, and blinding (masking) of participants and providers cannot be implemented except for data analysts who will handle the study data independently. The study clusters will include all consecutive and eligible participants until the total sample size of 7920 participants is reached.

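### The statistical analysis section promises to account for clustering, but the only between-arm tests it names treat women as independent although centres are randomised in matched trios

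*Protocol article*

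**What the plan says.** All references are to the protocol article.

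- **Randomisation.** Whole centres are allocated: "In each country, a total of 36 sites will be selected and matched into 12 trios", and within each trio "the study sites will be randomly assigned to one of three study arms at a 1:1:1 ratio". Women are then enrolled consecutively "until the total sample size of 7920 participants is reached".
- **Statistical analysis, clustering.** "Participants will form the unit of analysis and the clustered nature of the data will be accounted for". No technique is attached to this promise.
- **Statistical analysis, tests.** Changes between the 6-month and 12-month measurements are to be compared between control and each experimental arm. Chi-squared is named for categorical outcomes and Student's t for continuous ones: "tests for two independent proportions will be used, and for continuous variables, Student’s t-tests for two independent means will be used". No other between-arm method is named, and the trios are not mentioned.
- The same section promises a comprehensive statistical analysis plan and reporting under the CONSORT extension for cluster studies.

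**The concern.** Two statements in one paragraph do not fit together. The first says that clustering will be handled with the woman as the unit of analysis. The second names two tests whose standard form, applied to women, has no term for centre or trio. Someone who follows the named tests literally runs an analysis that ignores the design. Someone who adjusts for clustering departs from the published tests.

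Correlation within centres is plausible here. Counselling is delivered by each centre's own providers, and autonomy is judged from the client's encounter with them. At stake is the comparison of each experimental arm with control, on which any case for scaling up the package in two countries would rest.

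**Working it through.** **Inputs from the article.** There are 36 centres per country in 12 trios, so 12 centres per arm per country. Over two countries that is 72 centres, 24 trios and 24 centres per arm. The total is 7920 women.

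**Assumed, because the article gives no figure.** Two-sided alpha of 0.05; a range of intracluster correlations (ICC); 7920 covering both countries, which is how the Abstract reads. The article states no type I error, power, ICC or design effect, so there is no figure of its own to reproduce.

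**Women per centre.** m = 7920 / 72 = 110. This is an average.

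**Outcome levels at one time point.** Design effect DE = 1 + (m − 1) × ICC. Type I error of the unadjusted test = 2 × [1 − Φ(1.96 / √DE)]. The correct interval is √DE times as wide as the unadjusted one.

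| ICC | DE | √DE | Type I error |
|---|---|---|---|
| 0.001 | 1.109 | 1.05 | 6.3% |
| 0.005 | 1.545 | 1.24 | 11.5% |
| 0.01 | 2.09 | 1.45 | 17.5% |
| 0.02 | 3.18 | 1.78 | 27.2% |
| 0.05 | 6.45 | 2.54 | 44.0% |

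Simulation under the null (2000 runs per setting, 24 centres per arm) agreed. At ICC 0.01, 0.02 and 0.05 the t-test rejected in 18.6%, 27.0% and 44.4% of runs; the two-proportion test, with a true proportion of 0.4, rejected in 18.2%, 27.7% and 42.8%.

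**Sensitivity for levels.**
- If matching removes half the between-centre variance, the simulated error is about 12%, 18% and 31% at ICC 0.01, 0.02 and 0.05.
- With 50% loss to follow-up (m = 55), it is 11.4% at ICC 0.01 and 30.8% at 0.05.
- If 7920 were per country (m = 220), it is 27.3% at ICC 0.01 and 57.1% at 0.05.

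**6-to-12-month changes, the quantity the section actually compares.** Set the total variance at one time to 1, with stable centre variance 0.05, centre-by-time variance s, residual variance 0.95 − s, and within-woman residual correlation r. Subtraction removes the stable centre effect. The change then has between-centre variance 2s and within-centre variance 2(0.95 − s)(1 − r), so

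ICC of change = s / [s + (0.95 − s)(1 − r)].

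With m = 110 and r taken as 0 or 0.5:

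| s | ICC of change (r = 0; 0.5) | DE | Type I error |
|---|---|---|---|
| 0 | 0; 0 | 1; 1 | 5.0%; 5.0% |
| 0.005 | 0.0053; 0.0105 | 1.57; 2.14 | 11.8%; 18.0% |
| 0.02 | 0.0211; 0.0412 | 3.30; 5.50 | 28.0%; 40.3% |

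**Does respecting the design cure it?** In the same simulations of levels, a t-test on centre means (paired when matched) rejected in about 4.5% to 5.6% of runs for ICC 0.01 to 0.10.

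**The case against.** The strongest reply is that the sentence on clustering governs the paragraph. Cluster-adjusted versions of both tests exist, and a condensed article may name a family of tests and leave the adjustment to the analysis plan. Part of this stands. The authors evidently intend to adjust, and silence about the technique alone would be no finding. But the article is not silent: it names tests for independent samples, applied to participants, with no qualifier. A t-test on centre means would respect the design, but the unit-of-analysis sentence points away from it.

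Three stronger readings are tempting and are not supported.

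- *The trial will ignore clustering.* The article says the opposite. The error arises only if the tests are run as named.
- *False positives are inflated several-fold.* The article gives neither alpha nor ICC. For levels the inflation is 3.5-fold at ICC 0.01 but only about 1.3-fold at 0.001. For the planned changes, stable differences between centres cancel, and with no centre-by-time variance there is no inflation from clustering. Matching and loss to follow-up lower the figures further; a per-country reading of 7920 raises them.
- *Chi-squared cannot fit a change in a binary outcome.* Comparing between arms the proportion of women whose status changed is a coherent two-sample comparison, clustering aside. The article does not define the binary change, which is an ambiguity and not a demonstrated error.

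**Conclusion.** The inconsistency is certain from the text: cluster adjustment is promised, and standard independent-sample tests on women are named as the between-arm analysis of a trial that randomises centres in trios. It needs correcting because these tests carry the main comparisons.

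The numerical consequence is conditional on unadjusted use, two-sided alpha 0.05 and 110 women per centre. The type I error then lies between about 6% and 44% for outcome levels over ICC 0.001 to 0.05, before any gain from matching. For the planned changes it lies between 5% and about 40% over centre-by-time variance of 0 to 0.02 of the total. The article does not allow a choice within these ranges, so no single inflation figure should be quoted.

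**What to change.** In Statistical analysis, replace the two tests as the inferential method with a cluster-adjusted participant-level analysis. A mixed model or GEE with centre as the cluster would do, with:

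- terms for the matched trio, which also cover country because trios are formed within country;
- a small-sample correction suited to 24 centres per arm, or 12 per arm in country-specific analyses;
- allowance for repeated measurements on the same woman where several visits are modelled together.

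A trio-matched analysis of centre summaries is a valid alternative, but the unit-of-analysis sentence would then have to change to match. Chi-squared and t-tests can stay for description only.

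The cost is wording in the article and the analysis plan. No further centres, women or data are needed to make the correction. The downside is that intervals become wider, but correct, and some comparisons that would have looked significant may not be.
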